## HIV, obesity and insulin resistance

Worldwide and locally, there is evidence of increased obesity in high HIV endemic regions. The presence of obesity defined by a body mass index (BMI) equal to and above 30 kg/m2 increased from 34.4% to 47% in the first 3 years after HIV acquisition in a Durban study ([31](#_ENREF_31)). Locally it has been shown that obesity is markedly increased in South African black females compared to males ([26](#_ENREF_26), [32](#_ENREF_32)). Obesity and adipokine imbalance in PLWH have been shown to contribute to glucose disorders resulting in an incline in the prevalence of diabetes mellitus and other disorders of insulin-glucose homeostasis in PLWH ([33](#_ENREF_33), [34](#_ENREF_34)). The use of ART can lead to insulin resistance directly at a cellular level and indirectly via lipotoxicity ([35](#_ENREF_35)). The widely utilized NNRTI, Efavirenz, compared to an integrase inhibitor, Raltegravir, led to greater fat gain and has been shown to impair adipogenesis and induce pro-inflammatory cytokine production ([36](#_ENREF_36)).

## Other risk factors for CVD

Microalbuminuria is a well-known independent risk factor for cardiovascular disease though the exact mechanism is unclear ([37](#_ENREF_37)). It is most likely elevated due to chronic inflammation and endothelial dysfunction, which is exacerbated by HIV and ART. Measuring high sensitivity C-reactive protein (hsCRP) has been shown to add value to models predicting CVD events in HIV and was demonstrated to be an independent predictor of heart attack and stroke in women ([38](#_ENREF_38)). Levels less than 1, 1 to 3, and greater than 3 mg/L suggest lower, moderate, and high relative risk of CVD. EFV has been associated with a higher increase in hsCRP compared to other ART ([39](#_ENREF_39)).

## CVD risk assessment tools in HIV

A recent recommendation by WHO is the conduct of a cardiovascular risk assessment in PLWH ([40](#_ENREF_40)). The commonly used cardiovascular risk assessment tools do not consider HIV infection, ART type, duration of ART and younger age of PLWH. Cardiovascular risk has therefore been underestimated in PLWH especially younger PLWH ([7](#_ENREF_7)). The most widely used Framingham cardiovascular risk assessment tool has been to some extent, successfully used in PLWH in high income settings, however this tool has does not account for LMIC, and are most often administered in older persons with already well established disease ([41](#_ENREF_41)).

The Data collection on Adverse effects of anti-HIV Drugs (DAD) study includes a coronary heart disease (CHD) equation that calculates the absolute 5-year risk of CHD in PLWH. The DAD equation was developed in high-income countries and utilizes conventional risk factors and ARTs, indinavir, lopinavir/r and abacavir exposure to predict risk of CVD ([42](#_ENREF_42)). In a local study the DAD risk equation demonstrated a 31.1% moderate to high 5 year CVD risk, whereas when applying the Framingham equation only 6.7% moderate to high 10 year CVD risk was seen. Most participants had a low CVD risk by both risk equations in this cross-sectional study in rural SA([30](#_ENREF_30)).

The WHO PEN assesses CVD risk by means of the WHO and International Society of Hypertension (WHO/ISH) cardiovascular risk prediction charts specific to 14 epidemiological sub-regions ([43](#_ENREF_43), [44](#_ENREF_44)). These guidelines have been developed in order to identify people who are at a 10 year risk of developing a major cardiovascular event based on age, gender, systolic blood pressure, presence of diabetes mellitus, total blood cholesterol and tobacco use. Risk assessment begins at age of 40. CVD risk may be higher than indicated by the charts in persons already on antihypertensive therapy, who are obese and who have a sedentary lifestyle. Family history of premature CHD or stroke, elevated triglycerides, low HDL, elevated C-reactive protein, presence of microalbuminuria, tachycardia, fasting glycaemia or impaired glucose tolerance, and socioeconomic deprivation may also indicate a higher risk. Being specific to sub-regions, the WHO/ISH cardiovascular risk is a more suitable CVD risk assessment tool in our setting. Studies assessing the WHO PEN intervention in the general population have shown that it is a feasible management plan in reducing cardiovascular risk([45](#_ENREF_45)). However HIV risk is not factored in and the age of risk assessment should ideally begin at a younger age.

## CVD risk assessment in young adults

The large prospective CARDIA study has shown that young adults with detectable risk factors at baseline, were 2 to 3 times as likely to have coronary artery plaque calcification suggesting that intervention when risk factor levels reach management guideline thresholds may be too late in preventing CVD ([46](#_ENREF_46)). In a large South African study, the prevalence of multi-morbidity (MM) namely HIV, Diabetes and Hypertension in HIV-infected persons in the 18–35 and 36–45 age groups was higher than the patients not on ART, with a higher MM prevalence in the youngest age group in females versus male patients ([24](#_ENREF_24)). HIV and ART cause premature ageing, reiterating the need for an earlier risk assessment and primary intervention ([47](#_ENREF_47)).

## Measurements of subclinical atherosclerosis

There is an increased prevalence of subclinical atherosclerosis in HIV infected people compared to HIV uninfected([48](#_ENREF_48)). Measurement of carotid intima media thickness (CIMT) by ultrasound is a non-invasive method of detecting subclinical atherosclerosis. In a local study of predominantly women, there was a 12% prevalence of subclinical atherosclerosis (CIMT >0.78 mm) which was associated with traditional risk factors of CVD rather than HIV-specific factors ([49](#_ENREF_49)).

## Current CVD risk modification in HIV

Despite all that is known, there is a lack of integration in current HIV management and cardiovascular prevention/management guidelines in South Africa. Integration of HIV and Non-communicable diseases (NCD) testing in rural Uganda and Lesotho identified a high number of undiagnosed HIV, hypertension and diabetes([50](#_ENREF_50)). Chronic care models in HIV supported by USAID have been implemented in Kenya, Nigeria and Zambia ([41](#_ENREF_41), [51](#_ENREF_51)). In South Africa, a good way to start from a practicality view point is the Essential Drug Lists (EDL PHC). The EDL has dedicated chapters on both management categories all in one convenient reference guide. However the patient receiving treatment at the HIV clinic usually has measurements of basic vital signs, for example, height, weight, temperature and blood pressure. If an abnormality is detected, they are usually referred to a different department or institution for the management of non-communicable diseases, in a silo fashion. Current local HIV guidelines recommend a blood pressure (BP) measurement, urinalysis for glycosuria, serum creatinine at HIV diagnosis and ART initiation. A fasting cholesterol and triglycerides blood is analysed if the individual requires Lopinavir or other PIs. Thereafter there is no recommendation for screening of BP, glucose, cholesterol and other risk factors of cardiovascular disease (CVD) in the follow-up plan of persons on antiretroviral therapy (ART) in the National HIV treatment guidelines. There is minimal data available assessing the outcomes in PLWH who receive a comprehensive integrated HIV and NCD treatment package and there are no studies comparing institutions who provide integrated treatment versus compartmentalized treatment. The WHO ICCC model and SA Integrated Chronic Disease Management are proposed frameworks currently not implemented ([52](#_ENREF_52)).

## Rationale

South Africa has begun rolling out the Universal test and treat guidelines attempting to valiantly halt the high incidence of HIV. However despite longer life expectancy, PLWH have a higher risk of death compared to HIV uninfected persons due to presence of NCDs, especially from atherosclerotic CVD. The main emphasis of management in South Africa and other low and middle-income countries is on communicable diseases and there is a lack of reinforcement of structured chronic non-communicable diseases (NCD) guidelines and monitoring, with scanty statistics on morbidity related to NCDs such as CVD. Cardiovascular disease is the leading cause of death in women and the risk is often underestimated in women([53](#_ENREF_53)). This study proposes to provide data on the prevalence and incidence of CVD risk factors in a cohort of HIV-infected women from a low income background, and highlight potential benefits of a cost-effective, fundamental set of evidence-based interventions for improving morbidity and mortality from CVD and it’s risk factors, that is achievable in LMICs from Primary Health Care (PHC) levels.

# conceptual framework

The conceptual framework for this study is based on the complex web of causes that lead to cardiovascular disease and its endpoints. The study aims to identify interactions between the well-known conventional behavioural, environmental and metabolic causes of CVD with HIV and ART.

Furthermore, the framework for integrated management of chronic multi-morbidity of non-communicable diseases (NCD) and infectious chronic disease (ICD) is based on WHO Innovative care for chronic conditions model (ICCC). The ICCC framework focuses on improving primary healthcare at three levels: micro level (individual and family), meso level (healthcare organisation and community), and macro level (policy). An adaptation of this model is by Oni et al, which incorporates the colliding epidemics of NCDs and ICDs.

MESO

MICRO

MACRO

WHO ICCC Framework modified by Oni et al([1](#_ENREF_1)) and further modified by the investigator for the purposes of this protocol

Policy Environment

Patients and Families

Health Care Team

Community

Partners

# research design and methods

## Overview

1. Study Setting: Umlazi/Philasande Research Clinic and Gateway Umlazi Clinic
2. Study Design: This study is a prospective two-arm, quasi-experimental design comparing a primary health care intervention plan with usual care.
3. Target Population: HIV infected women attending PHC
4. Study population: HIV infected women aged from 18 to 49 years of age and receiving HIV care at PHC clinics.
5. Inclusion criteria

- HIV infected women
- On ART for at least 1 year
- Equal to/older than 18 years of age
- Equal to/younger than 49 years of age
- Plans to remain in the study catchment area for at least 3 years

1. Exclusion criteria

- Participant declines study participation

1. Sampling

• Size of sample

400 HIV-infected women consisting of an intervention arm of 200 women co-enrolled in the PROMOTE study at the Umlazi CRS (see method of sampling for details), and a control arm of 200 women receiving HIV care at the PHC. With a 20-30% estimated prevalence of metabolic syndrome in people living with HIV without any specific intervention in the risk factor modification of cardiovascular disease and a proposed 10-15% estimated incidence of metabolic syndrome in the intervention arm, 132 participants per arm would allow for 80% power. An additional 10% can be added to allow for loss to follow-up. The larger proposed sample size will allow for external validity / generalizability.

- Method of selecting sample

Two HIV-infected female cohorts will be matched for receipt of ART duration >1 year and for age will be compared in the study. Method of selection will be via convenience sampling.

**Intervention group**: There are 245 HIV infected women between 18 and 49 years of age, who have been on ART for more than 1 year and attending the CAPRISA Research Clinic in Umlazi. These women were enrolled into the PEPFAR PROMise Ongoing Treatment Evaluation (PROMOTE) observational study from May-June 2017. This study has been implemented to provide long-term follow-up data on safety outcomes of widespread use of combination antiretrovirals (cART) among an already well-characterized cohort of HIV infected mothers and their children who previously enrolled in the multi-site PROMISE study. This cohort was selected for the proposed intervention arm because the principal investigator is based at the research clinic. Women will be briefed at their next PROMOTE study visit and the 1^st^ 200 interested candidates meeting all eligibility criteria will be co-enrolled into the Intervention arm of the Sub-study.

**Control group**: The Tier data base will be used to select HIV infected women aged between 18-49 years, receiving ART for more than 1 year at the Umlazi Gateway PHC. Scheduled clinic visits at similar time points to the anticipated clinic visits in the intervention group will be used to establish a list of potentially eligible women. Following a matched pool of data, the first 200 women fulfilling the inclusion criteria, who attend the clinic for their next appointment and who consent to study participation will be enrolled.

1. Data sources

- Intervention group: Each participant in the intervention group will be assigned a new Participant identifier number (PID) in addition to the PROMOTE PID. History taking and physical exam, as well as laboratory results and where applicable ultrasound reports, will be entered directly into a data collection tool on a Microsoft Excel spreadsheet (Appendix I).
- Control group: Participants will be assigned a PID in addition to their clinic chart number. Information from clinic patient medical records will be entered directly into the data collection tool (Appendix II). At the final study visit; history, physical exam, lab report finding and ultrasound findings (where applicable), will be source documented.

1. Measures to ensure validity

- Internal
- The prospective nature of the study, large sample size, careful matching between cohorts by age category and by duration of ART aims to counteract the potential for selection bias.
- Information bias in chart review will be controlled by training of staff involved in data collection. Missing information
- Loss to follow up – a retention plan will be place to send clinic appointment reminders by sms or whatsapp, telephone calls in the case of missed visits and occasionally home visits when deemed necessary.
- Laboratory sample measurements will be performed by a certified laboratory.
- External -The larger proposed sample size will allow for external validity / generalizability.

1. List of Variables to be measured and schedule of evaluations

| CVD risk factors | Intervention Arm  (at main study PROMOTE scheduled visits)  Year 1(0+6m), Year 2(12+18m), Year 3(24+30m), Final study Visit (36m) | Control Arm | |
| --- | --- | --- | --- |
|  |  | **Year 1, 2, 3 (not including end of study visit) | Year 3 (end of study-36months) |
| Non-modifiable | Age (Categories in 5 year) | Age (Categories in 5 year) | Age (Categories in 5 year) |
|  | Race (A, I, W, C, O) | Race (A, I, W, C, O) | Race (A, I, W, C, O) |
|  | Family history of CVD in first degree relatives |  | Family history of CVD in first degree relatives |
| Modifiable | Smoking (Current, Never, Past) |  | Smoking (Current, Never, Past) |
|  | Unhealthy Diet |  | Unhealthy Diet |
|  | Exercise (minutes per week) |  | Exercise (minutes per week) |
|  | ART duration in years | ART duration in years | ART duration in years |
|  | ARV regimen | ARV regimen | ARV regimen |
|  | Viral load | Viral load | Viral load |
|  | CD4 count | CD4 count | CD4 count |
|  | BMI (6monthly) | BMI (6monthly) | BMI |
|  | Waist Circumference (6 monthly) |  | Waist Circumference |
|  | Systolic BP (6monthly) | Systolic BP | Systolic BP |
|  | Pulse (6monthly) |  | Pulse |
|  | Fasting Glucose (annual) |  | Fasting Glucose |
|  | Fasting Lipogram (annual) | Fasting Lipogram | Fasting Lipogram |
|  | hsCRP (annual) |  | hsCRP |
|  | Urine Microalbumin (annual) |  | Urine Microalbumin |
|  | *Carotid intima media thickness |  | Carotid intima media thickness |
|  | CVD risk % by Framingham |  | CVD risk % by Framingham |
|  | CVD risk % by DAD |  | CVD risk % by DAD |
|  | CVD risk % by WHO/ISH |  | CVD risk % by WHO/ISH |

*Only at year 3 in women aged over 40 years **Data collection through chart review

1. Plan for Data collection

- **Intervention group**: The prevalence of CVD risk factors will be determined by data collection through history taking, physical examination, and laboratory and radiology investigations as per the data collection tool. CVD risk assessment will be performed annually using a combination of the WHO and International Society of Hypertension cardiovascular risk prediction (WHO/ISH) and the DAD CHD equation. The intervention proposed is a modified WHO PEN algorithm incorporated into HIV management guidelines at study entry. Trends in all risk factors will be monitored, and new risk factors identified, with 6 monthly intervention during the first year, and annually for three years thereafter.
- **Control group**: Following informed consent, data will be collected from the participants ARV clinic medical chart as per the data collection tool. Standard of care HIV management and primary health care will be provided by public sector clinic staff according to current national guidelines. No study investigations or study questionnaires will be carried out at entry visit until the final study visit. There will be regular telephonic follow up with the participants to maintain study retention. Chart review data collection at 6 monthly intervals. CVD risk factors, as per outcomes described above, will be measured by the study at a single 3 year final study visit. Information obtained will be conveyed to the clinic staff for further management if required.

1. Plan for Data handling/processing

- Data will be analysed using SAS or SPSS software

1. Statistical methods

- Descriptive statistics-continuous variables will be represented by means, medians, prevalence, standard deviation.

The categorical variables will be represented by N+%

- Analytic statistics

The continuous variables will be compared by use of t-tests or Wilcoxon rank sum tests.

The categorical variables will be compared using Chi sq or Fisher’s exact test/

- Logistic regression will be applied to identify predictors of cardiovascular disease between the two arms, and between those participants who exhibit atherosclerosis by carotid intima thickness and those who don’t.

1. List of possible confounders

- Women in the intervention group are already enrolled in a study with controlled settings. These women may have commenced ART with a higher baseline CD4 counts.
- Multivariate logression analyses will be utilized in order to control for confounders.

1. List of associations to be measured

|  | BMI | WC | Fasting lipogram | Systolic BP | Fasting  Glucose | Urine microalbumin | hsCRP | Carotid initima medial thickness |
| --- | --- | --- | --- | --- | --- | --- | --- | --- |
| Age | x | x | x | x | x | X | x | X |
| Family History  of CVD | x | x | x | x | x | X | x | X |
| Tobacco use | x | x | x | x | x | X | x | X |
| Diet | x | x | x | x | x | X | x | X |
| Exercise | x | x | x | x | x | X | x | X |
| ART regimen | x | x | x | x | x | X | x | X |
| ART duration | x | x | x | x | x | X | x | X |
| VL | x | x | x | x | x | X | x | X |
| CD4 | x | x | x | x | x | X | x | X |
| BMI |  |  | x | x | X | X | x | X |
| WC |  |  | x | x | X | X | x | X |
| Fasting Lipogram |  |  |  | x | X | X | x | X |
| Systolic BP |  |  |  |  | X | X | x | X |
| Fasting Glucose |  |  |  |  |  | X | x | X |
| U-microalbumin |  |  |  |  |  |  | x | X |
| hsCRP |  |  |  |  |  |  |  | X |
| CVD risk % by Framingham |  |  |  |  |  |  |  | X |
| CVD risk % by DAD |  |  |  |  |  |  |  | X |
| CVD risk % by WHO/ISH |  |  |  |  |  |  |  | X |

1. Calculate cardiovascular risk as per WHO –ISH, DAD and Framingham, annually in intervention group and in the control group at year 3 and compare short term outcomes (presence of subclinical atherosclerosis by means of CMIT, presence of stroke, MI, angina -ischaemic heart disease)

1. Intervention:

**DIETARY CHANGES:** All individuals encouraged to reduce daily salt intake by at least one third and, if possible, to <5 g per day, to eat at least 400 g a day of a range of fruits and vegetables as well as whole grains and pulses and to reduce total fat and saturated fat intake

**PHYSICAL ACTIVITY:** All individuals encourage to do at least 30 minutes of moderate physical activity (e.g. brisk walking) a day, through leisure time, daily tasks and work-related physical activity.

**WEIGHT CONTROL:** All individuals who are overweight or obese should be encouraged to lose weight through a combination of a reduced-energy diet and increased physical activity

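### The population is defined as women in PHC care, but the intervention arm is a research-clinic cohort; sample size cannot supply the claimed generalizability, and regression cannot remove the setting effect

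*Protocol*

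**What the plan says.** All of this is in the protocol, Research design and methods, Overview.

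- **Population.** Item 3 reads "Target Population: HIV infected women attending PHC". Item 4 reads "Study population: HIV infected women aged from 18 to 49 years of age and receiving HIV care at PHC clinics".
- **Intervention arm.** Sampling describes "an intervention arm of 200 women co-enrolled in the PROMOTE study at the Umlazi CRS". The source is 245 women "who have been on ART for more than 1 year and attending the CAPRISA Research Clinic in Umlazi", mothers who had taken part in the PROMISE study. The first 200 who are interested and eligible are taken. The reason given is: "This cohort was selected for the proposed intervention arm because the principal investigator is based at the research clinic". The schedule of evaluations places their assessments at PROMOTE visits.
- **Control arm.** 200 women are selected through the Tier database of a single PHC clinic and receive usual care there.
- **Selection.** Convenience sampling, with matching on age and ART duration only.
- **Generalizability.** Under both Size of sample and Measures to ensure validity: "The larger proposed sample size will allow for external validity / generalizability".
- **Confounding.** The first entry in the list of possible confounders is "Women in the intervention group are already enrolled in a study with controlled settings". Possibly higher baseline CD4 counts come next. The remedy given is "Multivariate logression analyses will be utilized in order to control for confounders".

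**The concern.** The protocol describes one population and recruits its intervention arm from another kind of source. It then makes two assurances that the design cannot honour: that numbers give external validity, and that regression deals with a listed confounder which is a property of the whole intervention arm.

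At stake is what a month-36 difference means. It would combine the effect of WHO PEN with that of research-clinic staff and visits, and with that of being a participant kept in long-term research. Under Ethical Considerations, intervention women are reimbursed through PROMOTE, whereas controls are reimbursed only at the final visit; this is another difference tied to setting. If items 3 and 4 and the generalizability sentences stand, a reader would apply the result to women in ordinary PHC care without being told that the intervention was delivered elsewhere.

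**Working it through.** **1. The plan's own sample size.** Inputs from Size of sample: metabolic syndrome 20-30% without intervention and 10-15% with it, 80% power, 132 per arm, 10% added for loss. Alpha is not stated; two-sided 0.05 is assumed.

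Formula: n = [z(0.975)·√(2p̄(1−p̄)) + z(0.80)·√(p1(1−p1) + p2(1−p2))]² / (p1−p2)².

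With p1 = 0.30, p2 = 0.15 and p̄ = 0.225: n = [1.960·0.5906 + 0.842·0.5809]² / 0.0225 = 121. With continuity correction it is 134, within 3% of the stated 132, so the figure is reproduced. Allowing for 10% loss, 132/0.9 = 147. The remaining step from 147 to 200 per arm adds precision only. Nothing in the calculation bears on whom the sample represents.

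**2. Who is sampled.** 200/245 = 81.6% of one research cohort, taken in order of interest. This fraction is no measure of bias. It shows that the arm is most of a particular cohort, not a sample of PHC attendees, and adding women from the same source would not change that.

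**3. Can regression separate setting from arm?** By the recruitment and delivery rules, the intervention is given at research-clinic visits (200 of 200) and usual care at the PHC clinic (200 of 200). Let A be arm, S delivery setting and X the measured patient factors:

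logit P(outcome) = b0 + b1·A + b2·S + g·X.

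Since S = A for every woman, the model reduces to b0 + (b1 + b2)·A + g·X. Only the sum b1 + b2 can be estimated, at any sample size. The coefficients g can be estimated for factors recorded in both arms: the schedule includes age, ART duration, regimen, CD4, viral load, BMI and systolic BP. For controls the schedule leaves family history, smoking, diet, exercise, waist, pulse, glucose, hsCRP and urine microalbumin blank until month 36, so differences already present at entry in these cannot be adjusted for.

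**4. What sample size does to a setting effect (illustration).** The documents give no setting effect, so a range is assumed: no true intervention effect, control rate 20%, 25% or 30%, 200 per arm, two-sided 0.05. The chance of a significant result is Φ{[d·√n − 1.960·√(2p̄(1−p̄))] / √(p1(1−p1) + p2(1−p2))}, where d is the setting difference and p2 = p1 − d.

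| Assumed setting difference | Control 20% | Control 25% | Control 30% |
|---|---|---|---|
| 3 points | 11.7% | 10.5% | 9.7% |
| 5 points | 25.9% | 22.2% | 20.0% |
| 10 points | 80.2% | 70.7% | 63.8% |

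Worked case, 20% versus 10%: at n = 200, (0.1·14.142 − 1.960·0.5050)/0.5 = 0.849, giving 80%. At n = 132, (0.1·11.489 − 1.960·0.5050)/0.5 = 0.318, giving 63%. The larger sample makes a false conclusion more likely, not less.

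**The case against.** The design is disclosed. The protocol names both clinics, calls itself quasi-experimental, states convenience sampling, gives the reason for choosing the cohort and lists the controlled setting as a confounder. That stands: the fault lies in the population label and the stated remedies, not in concealment.

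Several stronger readings are tempting, and the documents do not support them:

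- **That item 4 is false for the intervention arm.** The protocol does not say where PROMOTE women receive routine ART. If that is a PHC clinic, the label conflict softens. The assessments are still PROMOTE visits, and the cohort is still not a sample of PHC attendees.
- **That no control can be a PROMOTE member.** The only exclusion criterion is declining to take part. Delivery setting coincides with arm; complete separation by cohort membership is an inference.
- **That confounder control fails altogether.** It fails for setting. Regression is a legitimate tool for CD4 and the other patient factors recorded in both arms.
- **That the hypothesis and objectives claim PHC delivery.** The hypothesis speaks of an integrated model of HIV care, and the first primary objective of women receiving HIV care; primary health care appears there only in the title of the WHO package. The Rationale's remark about PHC levels most naturally describes the interventions. The overreach rests on items 3 and 4 and the two sample-size sentences.
- **That a difference between arms in CD4 or viral load would reveal a clinic effect.** The protocol already allows that baseline CD4 may differ, and the intervention is built into HIV management. A null result would not exclude a setting effect on metabolic outcomes either.

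**Conclusion.** The point holds in this limited form. The two generalizability statements are wrong as written. The population items do not describe how the intervention arm is recruited and assessed. The stated regression remedy cannot reach the setting confounder that the protocol lists first. The last conclusion is structural: it needs only that delivery setting coincides with arm, which follows from the recruitment and visit rules, and no analysis plan could change it.

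The size of the resulting bias cannot be taken from the documents. The figures of about 20-26% for a 5-point and 64-80% for a 10-point setting difference rest on assumed differences, no true effect, the protocol's 20-30% control range and two-sided 0.05. They show direction and scale and do not predict this trial's error rate.

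**What to change.** 1. Delete the sentence on external validity under both Size of sample and Measures to ensure validity.
2. Reconcile items 3 and 4 with the recruitment routes, and state where PROMOTE women receive their routine HIV care.
3. Define the contrast as WHO PEN delivered at research-clinic visits to a PROMOTE cohort versus usual care at one public PHC clinic, and limit the conclusion to that.
4. In the list of possible confounders, state that regression addresses measured patient factors only and cannot remove the effect of setting.
5. If CD4 and viral load are compared between arms, present the comparison as descriptive and not as a test for a clinic effect.

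This is a change of wording. Recruitment, data collection and the main analysis stay as they are. The cost is a narrower and less favourable claim.
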